#### Secondary outcome measures

3.5.2

##### Discontinuation

The rate of discontinuation of study medication for any reason during Step 1 and Step 2.The rate of discontinuation of study medication for any reason during periods outside Step 1 and Step 2.Occurrence of treatment cessation because of recovery from illness (CGI‐S score = 1 for more than 6 months and in case the patient and the treatment psychiatrist agreed to stop medication).

##### Efficacy

Change in the severity of depression as measured by PHQ‐9 (central rating), CGI‐S, and QIDS‐SR_16_ (on site).The proportion of responders. Responders will be defined as those who score a 50% or greater reduction from the baseline PHQ‐9 score.The proportion of remission. Remission will be defined as the PHQ‐9 score ≤ 4.

##### Health outcomes

Change in the level of quality of life as measured by the EQ‐5D (on site).Change in the level of functional impairment as measured by the SDS^44^ (central rating).

##### Safety

Change in the level of the global burden of side effects as measured by the FIBSER Scale (central rating).Spontaneously reported Adverse Events (AEs) report and Serious Adverse Events (SAEs) report (on site).The onset of manic/hypomanic/mixed episodes evaluated by a clinical assessment and confirmed by the M.I.N.I. (on site).ECGs (QTc) and laboratory analyses (CBC, TP, Alb, T‐Bil, AST, ALT, GGTP, BUN, Cre, T‐Chol, TG, Na, K, CL, and glucose).

##### AEs

Adverse events are defined as any undesirable experience in patients during the use of medication. Regardless of the relationship and causation to the medication, all AEs are monitored and recorded throughout the study by clinical evaluations and observations, the results of any clinical data, and clinical complaints. Serious Adverse Events are defined as any untoward medical occurrence that may happen at any dose:
Results in death.Is life‐threatening.Requires inpatient hospitalization or causes the prolongation of existing hospitalization.Results in persistent or significant disability/incapacity.Is a congenital anomaly/birth defect, orRequires interventions to prevent permanent impairment damage.

However, hospitalization not related to the exacerbation of the current mental illness, such as hospitalization for the coordination of social circumstances, judged by the treating psychiatrist, is not regarded as SAE. Treating psychiatrists record the name (defined in Medical Dictionary for Regulatory Activities, MedDRA), occurrence date, seriousness, grade, any intervention for AE (the name of the intervention if any), outcome, and relationship to the study medication into the electronic clinical research form (eCRF). If the symptoms already existed at the baseline and no exacerbation occurred during the study, they will not be treated as AEs.

Adverse events are graded into three categories in the present study:
Mild: asymptomatic or mild symptoms; clinical or diagnostic observations only; no intervention indicated; no effects on usual daily activities.Moderate: minimal, local, or non‐invasive intervention indicated; limiting age‐appropriate instrumental activities of daily living (ADL); some effects on usual daily activities.Severe: medically significant, life‐threatening, or relating to death; hospitalization or the prolongation of hospitalization indicated; disabling; limiting self‐care ADL; significant effects on usual daily activities.

Causality between AEs and the medication is judged by the treating psychiatrist as one of the following:
No causality: There is no time relationship between the occurrence and study drug, and it is supposed to be from the underlying disease, comorbidities, accidentally, medication other than the study drugs, or comorbid therapies.Possible: There is some time relationship, and it may not be from the underlying disease, comorbidities, accidentally, medication other than the study drugs, or comorbid therapies. Considering toxicity or the pharmacological action of the study drug, the relationship of the study drug cannot be excluded.Probable: There is some time relationship and it cannot be from the underlying disease, comorbidities, accidentally, medication other than the study drugs, or comorbid therapies. The toxicity or pharmacological action of the study drug clearly explains the relationship.Unclear: None of the above.

Outcomes are judged by the treating psychiatrist as follows:
Full recovery: disappearance of AE and the exact status as that before AE.Partial recovery: improvement in the degree of AE despite its existence.No recovery: no improvement or deterioration in the degree of AE.Full recovery with sequelae: disappearance of AE with some sequelae.Death: death.Unknown: unable to identify (such as due to a no‐show).

Procedures and interventions for AEs are as follows:
The treating psychiatrist will monitor and take responsibility for the patient's safety.If they judge that any intervention or treatment is necessary, the treating psychiatrist will explain to the subject the details of what he/she will do and the expected effects and risks.In addition to taking appropriate medical interventions, the treating psychiatrist will follow up the subject for a reasonable period of time, record the AE name, date of occurrence, seriousness, degree, degree of treatment, presence or absence of treatment, outcome, and causal relationship.If SAEs occur, the treating psychiatrist and principle investigator will report their details to the Institutional Review Boards (IRBs)/Ethical Committees (ECs) and DSMC immediately to follow their decision as to whether the study may be ethically continued and if the protocol and/or informed consent form need to be amended following SAEs.The contents of medical records will be reported to the study office by the treating psychiatrist or clinical research coordinator via the eCRF.At least annually, the principle investigator summarizes the status of the research, the occurrence of adverse events, and self‐assessments, and the clinical trial review committee or ethics review committee of each facility evaluates the research implementation status report.

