#### Primary outcome measures

3.5.1

The primary endpoint of the present study is the rate of discontinuation for any reason at week 52. The discontinuation of study medication will be further divided into seven subgroups based on the reason for discontinuation ascertained by the treating psychiatrist at the time of the subject's discontinuation and will be confirmed by the Data Safety Monitoring Committee (DSMC).
Discontinuation due to intolerance is deemed by the treating psychiatrist while its validity needs to be evaluated by the scores of FIBSER^46^ (Frequency, Intensity, and Burden of Side Effects Rating) and EQ5D.Discontinuation due to the lack of efficacy is applied when initiated by patients or their related persons claiming that the allocated drug is not effective and they want to stop using it.Discontinuation due to significant deterioration is defined as CGI‐I score ≥ 6 (worse or markedly worse) in two consecutive visits. Treating psychiatrists must stop using the allocated drug.Discontinuation due to consent withdrawal is applied when a written withdrawal form is submitted by the subject. Reasons for withdrawal will be further analyzed and may be reclassified to other reasons for discontinuation.Discontinuation due to other safety issues, such as gestation, accidents, or admission to hospital with a physical illness, is deemed by the treating psychiatrist or patients.Discontinuation due to a loss to the follow‐up for inevitable reasons such as moving.Discontinuation due to other reasons.

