## ETHICAL APPROVAL

The protocol Version 2.4 was presented to an IRB for approval (National Center of Neurology and [name]‐KN01). Following an initial review and approval (16 October, 2013), the local institutional IRBs/ECs will review the protocol. IRBs/ECs will review the protocol at least annually. The principal investigator will submit safety and progress reports to the IRBs/ECs at least annually and investigators in each site will submit reports within 3 months of study termination or completion at the local site. These reports will include the total number of patients enrolled, severe and non‐severe adverse events, and summaries of each data safety and monitoring board review of safety and/or efficacy. At the occurrence of SAEs, the principle investigator will immediately report the details of the incidence to the NCNP‐IRB and DSMC. All patients will give written informed consent (Appendix [Link]) prior to the baseline assessment. When necessary, DSMC plays a role to recommend to the sponsor whether to modify the trial protocol taking into consideration such factors like the safety, recruitment progress, and protocol compliance. In this case, the principal investigator may apply for IRBs/ECs to review the modified protocol after discussing the matter with other investigators.

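### As worded, the SAE exemption covers every admission not due to worsening of the current mental illness, so a physical-illness admission with no other seriousness criterion loses SAE status and immediate reporting

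*Protocol article*

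**What the plan says.** Section 3.5.2 of the protocol article, under AEs, lists the criteria that make an untoward medical occurrence serious. One of them is "Requires inpatient hospitalization or causes the prolongation of existing hospitalization", with no limit on the cause of the admission. Other criteria in the list, for example "Results in persistent or significant disability/incapacity", do not depend on admission.

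The next paragraph sets an exemption. The exempt class is "hospitalization not related to the exacerbation of the current mental illness, such as hospitalization for the coordination of social circumstances", and such an admission, "judged by the treating psychiatrist, is not regarded as SAE". No exception is made for physical illness or for events attributed to the study drug.

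Urgent reporting depends on SAE status. The procedures list in the same section has the treating psychiatrist and principal investigator "report their details to the Institutional Review Boards (IRBs)/Ethical Committees (ECs) and DSMC immediately". The Ethical Approval section repeats the trigger: "At the occurrence of SAEs, the principle investigator will immediately report the details of the incidence".

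Section 3.5.1 takes a different view of physical admissions. Among the safety reasons for stopping study medication it names "accidents, or admission to hospital with a physical illness".

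**The concern.** The exemption contradicts the hospitalisation criterion directly above it. The words before the example define a general class, and the example only illustrates that class. A site that follows the sentence literally would not class an admission for a physical illness as an SAE unless another criterion applied.

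Two things are at stake. The first is speed: the immediate report is what leads to a decision on whether the study may ethically continue and whether the protocol or consent form needs amending. The second is the SAE outcome, which Section 3.5.2 (Safety) lists among the safety measures. Counts by arm would omit these admissions.

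The call is also made by someone who knows the allocation. The abstract states that treating psychiatrists are unblinded, and the exemption rests on their judgement. Classification could therefore differ between arms, although nothing in the document shows that it did.

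**Working it through.** No figure is involved, so the check applies the two rules in Section 3.5.2 (AEs) to four kinds of admission and then follows the one on which they disagree.

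1. **Social admission with no medical event.** There is no untoward medical occurrence, so the SAE definition is not met. The exemption gives the same answer. No conflict.
2. **Admission for worsening depression.** The hospitalisation criterion makes it an SAE, and the exemption does not reach it. No conflict.
3. **Admission for a physical event that is also fatal, life-threatening or disabling, or that needs intervention to prevent permanent impairment.** The exemption speaks only of hospitalisation, so the event stays an SAE under the other criterion. No conflict in outcome.
4. **Admission for a physical event that meets no other criterion.** The hospitalisation criterion makes it an SAE. The exemption removes it, because the admission is not related to worsening of the current mental illness. The two rules contradict each other.

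Following case 4 through the rest of the document, with the exemption applied as written:

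- **AE record:** kept. All AEs are recorded whatever their cause (Section 3.5.2, AEs).
- **Grade:** severe. That grade includes events for which hospitalisation is indicated (same section).
- **Immediate report to ethics committees and DSMC:** not triggered. Both statements of the rule require an SAE (procedures list; Ethical Approval).
- **SAE outcome:** absent from the count (Section 3.5.2, Safety).
- **DSMC safety review:** still possible, at intervals (Section 3.6.5) and after 100 registered patients (Section 3.6.4). Neither review is limited to SAEs.
- **At-least-annual reports:** included, since these cover adverse events (procedures list; Ethical Approval).
- **Discontinuation reason:** confirmed by the DSMC, but only if study medication is stopped (Section 3.5.1).

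The loss is therefore confined to SAE status, the immediate report and the SAE count, and it arises only in case 4.

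**The case against.** The strongest reply is that the intent was narrower. The only example is a social admission, which is not an untoward medical occurrence at all, so the authors may have meant to exempt only admissions of that kind. The article also condenses a full protocol (Version 2.4) that is not shown, and site practice cannot be known from it. This stands as a caution about what happened in practice. It does not repair the sentence, which states a rule in general terms; the problem is not a detail left out by condensation.

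A second reply is that these events remain visible. This largely stands. A reader might infer that the DSMC and the interim safety review would be blind to physical admissions. The document does not support that, because AE recording, the severe grade, DSMC review of safety data and the periodic reports all remain. QTc, the physical harm that the Background flags for escitalopram, is also followed by ECG as a safety outcome in its own right. A periodic summary is still not the immediate report that the procedures list requires.

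Three other inferences should be resisted:

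- The exemption does not contradict the rule that AEs are recorded regardless of causation. That rule governs recording, and the exemption changes only SAE status.
- Not every drug-related admission loses SAE status. Events that meet another criterion keep it.
- A count of lost SAEs cannot be given. Assuming that 1% to 5% of the 242 planned patients have a non-psychiatric admission gives 242 × 0.01 = 2.4 to 242 × 0.05 = 12.1 patients. That rate has no basis in the document, and the product includes events that would stay serious under another criterion and planned admissions that are properly exempt.

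**Conclusion.** The point holds as a contradiction in the stated SAE definition. Read literally, the exemption strips SAE status from any admission not related to worsening of the current mental illness. For a physical event whose only seriousness criterion is hospitalisation, this removes the immediate report to ethics committees and DSMC and the entry in the SAE outcome. It also fits poorly with Section 3.5.1, which treats admission with a physical illness as a safety issue.

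The size cannot be derived: the document gives no rate of physical admissions and no split by seriousness criterion. The conclusion rests on the literal wording and on the published text being the rule that sites followed. It concerns safety reporting and SAE counts. It does not touch the primary endpoint, the non-inferiority margin or the sample size.

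**What to change.** Reword the exemption in Section 3.5.2 (AEs) so that it covers only admissions without a new or worsened medical or psychiatric event, for example those for social circumstances or elective admissions planned before enrolment. State that every other admission, physical or psychiatric, is an SAE and follows the immediate reporting route in the procedures list. Reconcile the sentence with the safety category in Section 3.5.1.

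The Study Status section reports the study as accomplished in March 2018, so new wording cannot change reporting during the trial. The practical step is to review the hospitalised AEs in the eCRF, reclassify those that the exemption removed, and report SAEs by arm under the corrected definition, stating that this was done. Because the original calls were made by unblinded psychiatrists, the review is best done without knowledge of allocation.

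The cost is one sentence of text and a review of the AE records that involve an admission. Seriousness, grade and any intervention are already captured in the eCRF for each AE, so no new data collection should be needed.

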##### Methods of data collection and management

In the present study, all data, anonymized removing all obvious identifiers such as name, address, will be entered electronically via online clinical data capture, named the CR system. Original study forms will be filed and stored in locked cabinets at each participating site. They will be adequately stored for 5 years after completion of this study. Access to these forms will be properly restricted. Access to the data entered will be logged and restricted by identification codes and passwords. Data to be collected at each visit will be reviewed timely in order to check for inconsistencies by the data manager at the NCNP. The study sites are responsible for making appropriate corrections to the original paper forms whenever any item will be changed. Changes in electronic data will be preserved and traceable via electronic data capture and audit trails.

Data collection forms and required information will be discussed, and coordinators will be trained on how to code symptoms, events, and diseases using MedDRA software. They will also learn to enter data, respond to queries regarding data discrepancies, obtain general information, and arrange it into research quality data during training.

### Statistical analysis

3.6

#### Sample size calculation

3.6.1

The sample size needed will be 242 (n = 121 per group) in order to demonstrate the non‐inferiority of escitalopram to duloxetine with respect to the proportion of patients who discontinue the study at week 52. The sample size is based on the findings of the MANGA meta‐analysis,^35^ which estimated the between‐group difference in the attrition rate at week 52 to be 8%, and the attrition rate of escitalopram at week 52 was inferred to be 49% according to a previous study.^20^ Using a non‐inferiority margin of 10%, 242 patients need to be enrolled in order to achieve a statistical power of .8 with one‐sided alpha = .05.^35^

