Escitalopram is one of the antidepressants that have been categorized as SSRI, the mechanism of action of which is presumed to be linked to the potentiation of serotonergic activity in the central nervous system resulting from its inhibition of the neuronal reuptake of serotonin. Escitalopram is the S‐enantiomer of citalopram, which exhibits weak affinity for receptors other than serotonin.^16^ The efficacy of escitalopram for MDD was demonstrated in several acute 8‐week placebo‐controlled studies,^17^, ^18^, ^19^ and another 52‐week double‐blind controlled study showed that escitalopram was safe, well tolerated, and reduced the risk of relapse in long‐term treatments.^20^ Common side effects of escitalopram are nausea, headaches, dry mouth, and somnolence. In addition, a dose‐response relationship with an increased QTc interval was reported for escitalopram, albeit with a modest magnitude, in a large pharmacovigilance study.^21^

Previous findings suggest that SNRI have inherently greater efficacy than SSRI as a class.^22^, ^23^, ^24^, ^25^ Duloxetine selectively binds to norepinephrine and serotonin (5‐HT) transporters, but lacks affinity for other monoamine receptors within the central nervous system.^26^ Common side effects include nausea, headaches, dry mouth, and insomnia.^27^ The efficacy and safety of duloxetine in the acute treatment of MDD have also been established in several placebo‐controlled studies^28^, ^29^, ^30^ and one long‐term, 52‐week open‐label study.^31^

Three randomized controlled trials (RCTs)^32^, ^33^, ^34^ directly compared escitalopram and duloxetine and a meta‐analysis synthetizing the two antidepressants,^35^ and the findings obtained suggested that escitalopram has better efficacy (OR: 1.30, 95% confidence interval (95% CI): 0.88‐1.91) and a lower dropout rate (OR: 0.52, 95% CI: 0.26‐1.01) than duloxetine. However, two^33^, ^34^ of the three RCTs were conducted by the pharmaceutical company that developed escitalopram, while the other^32^ was conducted by the company that developed duloxetine. One RCT^33^ conducted by the pharmaceutical company that developed escitalopram applied an imbalanced design with flexible dosing on escitalopram and fixed dosing on duloxetine, resulting in attrition rates for escitalopram and duloxetine of 13.1% and 30.8%, respectively. In contrast, a network meta‐analysis among 12 antidepressants showed a small difference in the dropout rate between escitalopram and duloxetine (NNH = 20).^35^

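### The 8-point planning difference is not reconciled with the other figures cited from the same reference, and 80% power at one-sided .05 follows from neither 8 nor 5 points

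*Protocol article*

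**What the plan says.** Section 3.6.1 (Sample size calculation) fixes the size: "The sample size needed will be 242 (n = 121 per group"). It takes the assumed effect from a meta-analysis, reference 35, "which estimated the between‐group difference in the attrition rate at week 52 to be 8" percentage points. The other inputs are that "the attrition rate of escitalopram at week 52 was inferred to be 49% according to a previous study", a margin of 10%, power .8 and one-sided alpha .05. Section 3.6.2 repeats one-sided .05. Section 3.6.3 tests the upper limit of a one-sided 95% confidence interval for escitalopram minus duloxetine, using the normal approximation.

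The Background cites reference 35 for two other results on dropout. The first is that escitalopram had "a lower dropout rate (OR: 0.52, 95% CI: 0.26‐1.01) than duloxetine". The second, introduced as a contrast with a company-run trial, is a network meta-analysis that "showed a small difference in the dropout rate between escitalopram and duloxetine (NNH = 20"). Neither is given a time point.

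**The concern.** One reference is the cited source of three differences: 5 points (NNH = 20), 8 points (3.6.1), and about 16 points (the odds ratio applied to 49%). The article does not say how the 8 was reached or how it relates to the other two. It does say that the meta-analysis estimated 8% at week 52.

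This input drives the calculation. With a 10-point margin, an assumed 8-point advantage for escitalopram widens the distance being tested from 10 to 18 points. Section 3.6.1 speaks only of a between-group difference, yet the size works only if escitalopram is the better drug. A reader interpreting a failure to show non-inferiority needs to know how far the planned power rested on that assumed advantage, and the single figure of .8 does not show it.

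**Working it through.** **Inputs.** From 3.6.1: n = 121 per group, escitalopram pE = .49, margin .10, power .8, one-sided alpha .05. Duloxetine pD is .57 at 8 points, .54 at 5 points and .49 at no difference.

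**Converting the cited figures**
- NNH = 20: 1/20 = .05, or 5 points.
- Odds ratio 0.52: the escitalopram odds are .49/.51 = .961. Then .961/.52 = 1.848, so pD = 1.848/2.848 = .649, a difference of about 16 points.

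**Formulas** (unpooled variance, normal approximation, as in the 3.6.3 test)
- n per group = [pE(1−pE) + pD(1−pD)] × (z₁₋α + z₀.₈)² / (.10 + pD − pE)²
- SE = √{[pE(1−pE) + pD(1−pD)]/121}; power = Φ[(.10 + pD − pE)/SE − z₁₋α]

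**The plan's own figure (49% v 57%)**
- At one-sided .05: n = (.2499 + .2451) × (1.645 + .842)² / .18² = 94.5, so 95 per group, 190 in total. This does not reproduce 242.
- At one-sided .025: n = 119.9, so 120 per group (240); with pooled variance 120.7, so 121 per group (242). This does reproduce it.
- A continuity correction at .05 gives about 106 per group.
- Inflating 95 for dropout reaches 119 to 121 only at about 20% to 21%. No such inflation is stated, and discontinuation is itself the endpoint.

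**Power with 121 per group**
- 8 points: SE = √(.4950/121) = .0640; .18/.0640 = 2.814; minus 1.645 gives 87.9%.
- 5 points: SE = √(.4983/121) = .0642; .15/.0642 = 2.337; minus 1.645 gives 75.6%.
- 0 points: SE = √(.4998/121) = .0643; .10/.0643 = 1.556; minus 1.645 gives 46.5%.

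The normal approximation is not the source of the gap. Exact binomial enumeration of the confidence-interval rule at .05 gives 88.2%, 76.3% and 47.4%.

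At one-sided .025, the level that reproduces 242, the corresponding normal-approximation powers are 80.4%, 64.7% and 34.3%.

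**Other reference points**
- At one-sided .05, 121 per group reaches 80% at an advantage of about 5.9 points. 80% power at 5 points would need 137 per group.
- If escitalopram were 8 points worse (49% v 41%), power would be about 9%. The direction is therefore essential to the size.

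**The case against.** A reader might infer that the trial was underpowered at the effect its own Background reports. The documents do not support that, for three reasons.

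First, NNH = 20 carries neither a time point nor a baseline rate, and a risk difference need not stay at 5 points when attrition rises to 49%. Suppose, as an assumption, that the 5 points arose at escitalopram dropout of 13%, 17%, 20%, 25% or 30%. Holding the odds ratio constant, the difference at 49% becomes 9.5, 8.0, 7.2, 6.3 or 5.7 points, and power at one-sided .05 becomes 92%, 88%, 85%, 81% or 79%. An 8-point difference at week 52 could therefore be a reasonable extrapolation of NNH = 20.

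Second, 8 points is not the largest value the article offers. It corresponds to an odds ratio of (.49/.51)/(.57/.43) = 0.72, inside the reported interval of 0.26 to 1.01, and it lies between the 5 and 16 points obtained above. At 16 points power is about 99%.

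Third, the article plans and tests at one-sided .05. The lower powers at .025 are not the plan's powers; they matter only because 242 fits that level. At the stated alpha, the least favourable reading of NNH = 20 costs about 4 points of power.

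The direction can also be pieced together: the Background gives escitalopram the lower dropout, and 3.6.3 fixes the sign of the contrast.

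These arguments limit the point without removing it. The article does not describe the 8% as an extrapolation; it attributes it to the meta-analysis as an estimate at week 52. None of the arguments makes .8 the right power for 8 points at one-sided .05.

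**Conclusion.** The point holds as one of unreconciled inputs and a misstated power. Three differences (5, 8 and about 16 points) trace to one reference without explanation, and 3.6.1 omits the direction. At the stated one-sided .05 with 121 per group, the power is 87.9% at 8 points, so the plan's own inputs give more than it claims and 80% would need only 95 per group. It is 75.6% at 5 points, about 4 points less than claimed, and 46.5% at no difference.

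The 5-point result assumes that NNH = 20 is a week-52 difference, which the article does not say. All results assume escitalopram attrition of 49% and the normal approximation. That 242 came from one-sided .025 is an inference from the match (240 unpooled, 242 pooled, 80.4% power), not something the article states.

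**What to change.** In 3.6.1:
- State the assumed rates with their direction: escitalopram 49%, duloxetine 57%.
- State how 8% was derived from reference 35 and how it relates to the NNH of 20 and the odds ratio of 0.52 in the Background. If it is an extrapolation to week 52, label it so and do not call it the meta-analysis estimate.
- Replace the single .8 with power at one-sided .05: 88% at 8 points and 76% at 5 points, optionally 46% at no difference.
- State which alpha produced 242.

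The cost is one paragraph. Enrolment does not change; the article reports the study as accomplished in March 2018. The downside is a less favourable power figure at the smaller difference, while the figure at 8 points rises.

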#### Statistical analysis plan

3.6.2

Details on statistical analyses are specified in the statistical analysis plan (SAP) prepared and finalized before the analysis, although the basic policy is to compare groups for the items described below. The significance level in testing the primary non‐inferiority hypothesis is one‐sided .05 and that for all other secondary endpoints is one‐sided .05.

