#### Primary analyses

3.6.3

The primary analysis population in this study is ITT (intention to treat). All patients enrolled in this study need to be included in the analysis, except those who did not take the study medication.

Acceptability—Our primary endpoint is attrition and withdrawal rates from the allocated treatment for any reason at week 52. The non‐inferiority of escitalopram to duloxetine will be tested using the one‐sided 95% CI for the between‐group difference in the discontinuation rate (escitalopram − duloxetine). The CI is estimated with the normal approximation. If the upper limit of the one‐sided 95% CI is less than the non‐inferiority margin (Δ = 10%), escitalopram is considered to be non‐inferior to duloxetine in the primary endpoint.

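### On the stated inputs, 121 patients per group gives about 88% power at one-sided alpha .05, not 80%; the size matches one-sided .025

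*Protocol article*

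**What the plan says.** Section 3.6.1 of the protocol article fixes every input to the calculation:

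- Size: "242 (n = 121 per group", equal allocation.
- Expected difference: a cited meta-analysis "estimated the between‐group difference in the attrition rate at week 52 to be 8" percentage points.
- Escitalopram rate: "the attrition rate of escitalopram at week 52 was inferred to be 49" per cent, inferred from a previous study.
- Margin: 10 percentage points.
- Power and alpha: "242 patients need to be enrolled in order to achieve a statistical power of .8 with one‐sided alpha" of .05.

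Section 3.6.2 repeats the alpha: "The significance level in testing the primary non‐inferiority hypothesis is one‐sided .05". Section 3.6.3 gives the matching decision rule: "The non‐inferiority of escitalopram to duloxetine will be tested using the one‐sided 95% CI" for escitalopram minus duloxetine, computed by normal approximation, with success if the upper limit is below 10%. No allowance for dropout is stated, and one-sided .025 appears nowhere.

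**The concern.** Alpha, power, assumed rates and margin together determine the sample size. Here the usual formula at the stated alpha gives a clearly smaller number than the one stated, while the stated number appears at half that alpha. So alpha .05, power .8 and 121 per group cannot all be true on these inputs.

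Two things are at stake. First, a reader cannot tell whether the trial was designed with 80% or 88% power, or whether some 50 more patients were planned than the stated test needs. Second, if the designers worked at .025, the primary test as written is not the one they sized for, and some results would pass one rule and fail the other.

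**Working it through.** **Inputs.** Escitalopram rate 0.49, difference 0.08, margin 0.10, power 0.80, 1:1 allocation (all from 3.6.1). The duloxetine rate is derived as 0.57. The article does not spell out the direction, but the other one is not feasible: with escitalopram 8 points worse (0.49 v 0.41), the distance to the margin is 0.02 and n = 6.183 × (0.2499 + 0.2419) / 0.0004, about 7,600 per group.

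**Formula.** n per group = (z_α + z_β)² × V / d², where

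- d = 0.10 − (0.49 − 0.57) = 0.18, so d² = 0.0324
- V (unpooled) = 0.49 × 0.51 + 0.57 × 0.43 = 0.4950
- V (pooled, p = 0.53) = 2 × 0.53 × 0.47 = 0.4982

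**Attempt to reproduce 121 at the stated one-sided .05.** (1.645 + 0.842)² = 6.183.

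- Unpooled: 6.183 × 0.4950 / 0.0324 = 94.5, so 95
- Pooled: 6.183 × 0.4982 / 0.0324 = 95.1, so 96

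The total is 190 to 192, not 242.

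**At one-sided .025.** (1.960 + 0.842)² = 7.849.

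- Unpooled: 7.849 × 0.4950 / 0.0324 = 119.9, so 120
- Pooled: 7.849 × 0.4982 / 0.0324 = 120.7, so 121

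The pooled version gives 121 per group, 242 in total, exactly as stated.

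**Other variants at one-sided .05, per group.**

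| Variant | n |
|---|---|
| Pooled variance under the null, unpooled under the alternative | 95 |
| Farrington-Manning | 95 |
| Continuity correction | 106 |
| Rates 0.41 and 0.49 | 94 |
| No true difference (both 0.49) | 310 |
| 90% power | 131 |

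None gives 121.

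**Power with 121 per group.** SE = √(0.4950 / 121) = 0.0640, and 0.18 / SE = 2.814.

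- One-sided .05: Φ(2.814 − 1.645) = 87.9% (exact binomial enumeration of the decision rule: 88.2%)
- One-sided .025: Φ(2.814 − 1.960) = 80.4% (exact: 79.2%)

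**Type I error with 121 per group.** Exact enumeration with escitalopram exactly 10 points worse, at duloxetine rates of 47% and 57%:

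- Written one-sided .05 rule: 4.8% to 5.2%
- One-sided .025 rule: 2.3% to 2.6%

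**Largest observed difference that passes, using the planned-rate SE.**

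- One-sided .05: 10 − 1.645 × 6.40 = about −0.5 points
- One-sided .025: 10 − 1.960 × 6.40 = about −2.5 points

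An observed difference between these two values passes the first rule and fails the second.

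**The case against.** A reader might infer that the trial accepts false non-inferiority at twice the rate its size can support. That does not follow. The decision rule sets the type I error, not the number of patients. The written rule delivers about the 5% it declares, and 121 per group exceeds what that rule needs for 80% power by 25 to 26 patients per group. What is true is narrower: the rule allows twice the error of the level for which the size appears to have been computed.

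Nor does the article contradict itself on alpha. Sections 3.6.1 to 3.6.3 all say one-sided .05 or a one-sided 95% bound. The conflict is between the size and its own inputs within 3.6.1, and it understates power.

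It may also be objected that 121 could come from an unstated allowance at one-sided .05, since 3.6.1 speaks of enrolment and 3.6.3 leaves out patients who never took study medication. Dividing by 0.8 for 20% loss turns 95 into 119 and 96 into 120; the continuity-corrected 106 with 12% loss becomes 121. This cannot be excluded, but no allowance is stated, and discontinuation is itself the endpoint. One-sided .025 needs no unstated loss allowance or correction. It remains a strong inference, not a documented fact.

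Finally, moving the primary test to .025 is a design choice that the article does not compel. That stands, and it is why the alpha actually used has to be established first.

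**Conclusion.** The sample size statement is wrong as written. At the stated alpha, power is about 88% rather than 80%; put the other way, 80% power needs 190 to 192 patients rather than 242, an excess of 50 to 52. The size matches one-sided .025, which is the probable source.

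This rests on reading the 8 points as an absolute difference favouring escitalopram, on the normal approximation, and on no inflation. The choice of variance formula shifts the result by only one patient per group.

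The declared test remains valid at its declared level, and on its own assumptions the trial is not underpowered. The matter to settle is which of alpha, power and size is misreported.

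**What to change.** State in 3.6.1 which alpha and which variance formula the calculation used, and any allowance for loss, then bring 3.6.1 to 3.6.3 into line.

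- **If one-sided .05 stands:** restate 3.6.1 as about 88% power with 121 per group, noting that 190 to 192 patients in total would give 80%. In 3.6.3, note that the bound equals the upper limit of a two-sided 90% CI. The test does not change.
- **If .025 was intended:** set all three sections to one-sided .025, with the upper limit of the two-sided 95% CI below 10%. The 242 patients support this at about 80% power. The cost is a stricter hurdle: at the planned rates, the largest passing observed difference moves from about −0.5 to about −2.5 points.

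Neither route needs more patients. Because the Study Status section reports the study as accomplished in March 2018, the choice should rest on the record of the original calculation and not on the results.
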